**Figure 1 figure1:**
[figure not shown]
Flow diagram of study procedures. PosA: positive affect; EFT: episodic future thinking; ERT: episodic recent thinking.

### Participants and Setting

Participants will be recruited from the Charlotte, North Carolina, area community and asked to attend 2 in-person lab sessions separated by 5 days of daily diet tracking. The study will take place in a research lab in the Department of Psychology at the University of North Carolina at Charlotte, with a target recruitment of approximately 50% female. The United States Census Bureau provides estimates about the population characteristics in each state. Our race and ethnicity recruitment targets are derived from the Charlotte, NC 2017 Census [34]. To represent the Charlotte, NC population, we aim to recruit approximately 43% non-Hispanic white, 35% African American, 13% Hispanic or Latino of any race, 6% Asian American, and 3% other race (eg, Native Hawaiian or other Pacific Islander) or 2 or more races.

### Study Procedures

#### Identification

Potential participants will be recruited through postings in classified advertisement websites and on Facebook forums, through flyers posted at community buildings such as libraries and grocery stores, and through recruitment advertisements sent through university listservs reaching students, faculty, and staff. All individuals receiving this recruitment information will be considered potential participants.

#### Eligibility Assessment

Eligibility will be determined before coming to the lab by a Web-based screening questionnaire delivered via the Qualtrics survey platform. This survey will include basic demographic questions as well as self-reported height and weight (to calculate inclusion body mass index [BMI]) and questions assessing exclusionary medical conditions that could confound dietary choices (see below).

Participants are eligible if they:

Are aged between 18 and 63 years. We set the upper age limit at 63 years to limit the potential confounding effect of older age. Older adults may show a greater preference for immediate over delayed rewards [35], and this preference may be stronger among older adults with mild cognitive impairment [36-38] and Alzheimer disease [37,38]. On the other hand, other studies indicate that older adults may show a greater preference for delayed rewards compared with middle-aged adults [36]. In sum, TD may shift in older individuals as there is potentially less time in the future. Hence, our upper age limit is set at 63 years to minimize this age-related shift.Have a BMI indicative of overweight or obese status (BMI≥25 kg/m^2^), measured first through self-report and then verified at the baseline visit with anthropometric measurements.

Participants are ineligible if they:

Report any conditions that could affect their food choices (ie, special dietary conditions, including diagnoses of celiac disease or type 1 diabetes; are currently being treated for an eating disorder; have ever had gastric bypass surgery; are allergic to nuts or peanuts; or practice a vegan diet) or responses during the lab tasks.Have any devices (eg, pacemaker) in their body that could be disrupted by the bioimpedance scale measuring body fat percentage.Are currently pregnant.

#### Consent Procedure

Informed consent for the study will be obtained upon arrival at the study lab in a face-to-face interaction with trained research staff. The research staff will review study information with the participant to ensure good comprehension and understanding and to answer any questions for clarification. A waiver to allow withholding information about several portions of the study procedure during consent was obtained from the ethics board. First, we will not inform the participants that we will be recording their selection of unhealthy and healthy snacks. Disclosure of this portion of the study may bias participants to not select food naturally. Second, we will not be disclosing the BMI inclusion and exclusion criteria, as disclosure could significantly increase the prospective participants’ emotional distress as they could learn that they meet criteria for obese or overweight status. Third, we will not disclose inclusion and exclusion dietary health conditions that could impact food choice (eg, gluten intolerance, celiac disease, or type 1 diabetes). Finally, to ensure that participants are blind to intervention condition assignment, the consent form will not disclose the overall factorial design of the study, the number of intervention arms, or the intervention content.

### Ethics and Confidentiality

The study has been granted ethical approval by the Health Sciences Research Governance Committee, University of York (December 4, 2017), and the University of North Carolina at Charlotte Institutional Review Board (17-0388; October 6, 2017). A signed copy of the informed consent will be kept by the research staff, and a copy is available to the participants for their records.

### Randomization Process and Blinding

All questionnaires and intervention content will be delivered via the Qualtrics Web-based survey platform. After the consent is obtained, randomization will be achieved via the Qualtrics software randomizer function. Upon starting the experimental session on the computer, the Qualtrics survey will randomly deliver 1 of the intervention arms to each participant without any input needed from the researcher, resulting in double blinding. The consent information will only state that the participants will listen to a short recording instructing them to think about physical sensations or future events. There is no information provided in the consent form on the study design, and there is no mention of PosA, EFT, or the number of intervention arms. Therefore, both the researcher and the participant will be unaware of the intervention arm to which the participant is assigned. The Qualtrics randomization procedure will evenly present the 4 intervention arms or guided mental imagery schemes across participants.

### Intervention Content

Initial scripts for the interventions were developed and then presented to an advisory panel of professionals who are experts in guided mental imagery stimuli, affect manipulation, future episodic thinking, and eating from the United Kingdom and United States. Guided imagery scripts were also presented to 2 face-to-face community advisory panels, one in the United States and the other in the United Kingdom. The intervention development process is described in detail elsewhere [39].

During the guided imagery including PosA (arm 1 [PosA-EFT intervention] and arm 2 [PosA intervention]), participants will be invited to think of positive feelings and associations surrounding healthy fruits and vegetables. They will be asked to imagine themselves appreciating the healthy food and to bring awareness to the positive aspects of the food, such as its color, feel, smell, taste, and health benefits. Additionally, participants in the PosA-EFT intervention (arm 1) will then be invited to think in detail of a future where they have made healthy food choices. The EFT intervention (arm 3) focuses on future-oriented thinking as described above, but includes no positive emotions surrounding healthy food. Finally, the ERT intervention control (arm 4) asks participants to think about a recent event and aims to rule out potential effects of guided imagery alone on food decision-making and TD and to control for the effort involved in imagining an event at a different time than the present. The interventions will be delivered during the first experimental session (see the Experimental Sessions section below) using Qualtrics survey software to play the audio recording of the guided imagery for each of the 4 intervention arms.

### Quality Assurance of Treatment Delivery

The interventions are audio recordings that the participants will listen to during the first experimental session. Thus, they are standardized across all participants to ensure the consistent delivery of each intervention condition. After the intervention is delivered, 3 questions will be asked that function as intervention manipulation checks. Immediately after the intervention, participants will be asked to describe some of the thoughts that came to their minds while listening to the guided imagery recording. Next, participants will be asked to rate how positive and negative they felt *during the guided imagery* on a scale from 1 (“not at all”) to 10 (“extremely”). Participants’ written text responses, describing their thoughts during the intervention, will be blindly coded for the occurrence of PosA, EFT, and recent past episodic thinking.

### Training

A large team of approximately 6 research assistants, led by 1 or 2 trained lead research assistants, will implement the experimental procedures. A protocol manual will describe the entire experimental session and include information on how to guide the participant through the questionnaires and body measurements. Each research assistant will be trained multiple times in implementing the protocol. In addition, each assistant’s first scheduled participant session, for each time point, will be observed by 1 of the lead research assistants. Finally, follow-up drop-in observations will be scheduled periodically to maintain consistently accurate data collection.

### Experimental Sessions

The study protocol includes 2 in-lab experimental sessions separated by approximately 5 days of at-home daily food diary entries (see Table 1). All questionnaires, intervention content, and baseline and outcome measures are delivered via the Qualtrics Web-based survey platform. Participants will be asked to fast for 2 hours before each experimental session, and all sessions will be scheduled after 10:00 am.

During the first experimental session, the participants will complete a battery of questionnaires, a baseline TD task, and a baseline food demand task (see the Primary Outcome Measures section below). Then, they will be randomly assigned to receive 1 of the 4 guided imagery intervention arms followed by manipulation check questions. Next, they will complete the TD and food demand tasks again, after which they will be offered a variety of snack foods to assess food choice. Food items will be placed next to the participants while a research assistant reads a standardized food choice script. At the end of the session, the participants’ anthropometric measurements will be taken, they will be scheduled for the second experimental session, and they will be instructed on when and how to complete the daily food diaries. The duration of the first session will be approximately 90 min, and each daily food diary entry will take approximately 5 min to complete. During the second experimental session, participants will complete the TD and food demand tasks again. They will be asked to complete another battery of questionnaires while they are again presented with a variety of snacks to eat, to assess their food choices a second time. The duration of the second session will be approximately 40 min. The schedule of enrollment, interventions, and assessments for the study is shown in Table 1.

### Reimbursements

Participants will receive US $10 for completing the first experimental session, US $5 for completing at least 3 of the 5 food diaries, and another US $10 for completing the second experimental session, to compensate for potential participation-related expenses. Participants who do not complete all parts of the study (eg, they do not return for the second session) will only be reimbursed for the parts of the study they completed. Participants who complete all parts of the study will also be entered in a random drawing for a chance to win 1 of the 2 Target gift cards worth US $100.

**Table 1 table1:** SPIRIT Figure**:** Schedule of enrollment, intervention, and assessments.

Time point		Study period							
		Recruitment	Enrollment and allocation	Postallocation daily food surveys					Close out
		−t_1_	0	t_1_	t_2_	t_3_	t_4_	t_5_	t_6_
**Enrollment**									
	Eligibility screen	X	—^a^	—	—	—	—	—	—
	Informed consent	—	X	—	—	—	—	—	—
	Allocation	—	X	—	—	—	—	—	—
**Interventions**									
	Positive affect and episodic future thinking	—	X	—	—	—	—	—	X
	Positive affect	—	X	—	—	—	—	—	X
	Episodic future thinking	—	X	—	—	—	—	—	X
	Neutral affect and episodic recent thinking	—	X	—	—	—	—	—	X
**Assessments**									
	Baseline: TD^b^	—	X	—	—	—	—	—	—
	Baseline: Food demand	—	X	—	—	—	—	—	—
	Outcome: TD	—	X	—	—	—	—	—	X
	Outcome: Food demand	—	X	—	—	—	—	—	X
	Outcome: Food choice	—	X	—	—	—	—	—	X
	Outcome: Daily food surveys	—		X	X	X	X	X	—
	Assessments before allocation^c^	—	X	—	—	—	—	—	—
	Assessments after allocation^d^	—	X	—	—	—	—	—	—
	Assessments at close out^e^	—		—	—	—	—	—	X
	Repeated assessments (before allocation and at close out)^f^	—	X	—	—	—	—	—	X

^a^—: not applicable.

^b^TD: temporal discounting.

^c^Assessments before allocation: food frequency, reward-based eating, health-specific self-efficacy, weight related eating, health locus of control, perceived stress reactivity.

^d^Assessments after allocation: emotion regulation, trait mindfulness, behavioral motivations, impulsiveness, mental health history, physical health history, demographics.

^e^Assessments at closeout: global self-reported health, self-reported weight status, social desirability, coping responses, tobacco and alcohol use, sleep quality, loneliness, psychological flexibility.

^f^Repeated assessments (before allocation and at closeout): stages of change in weight management; *Covariate measures included in analyses*: perceived stress, positive and negative affect, and depressive symptoms.”

### Primary Outcome Measures

#### Temporal Discounting

The minute monetary TD task will be given at baseline, after allocation, and at closeout to assess TD. During the minute monetary TD task, participants answer 5 questions about their preference to receive specific monetary rewards over time (now vs later). Across consecutive trials, participants are presented with a fixed set of choices between smaller, immediate rewards and larger, delayed rewards (US $1000 in 3 weeks or US $500 now) with the temporal distance being adjusted at each trial (now, 4 days, 1 week, 3 months, and 2 years). The 5 questions are taken from a list of 64-item pairs with differential money and time options. The questions adjust based on the participants’ prior response to identify their delay discounting rate. For example, the participants select which option they would rather have “US $500 now” or “US $1000 in 3 weeks.” If the “US $1000 in 3 weeks” is selected, the next question will feature the same monetary reward at a more distant time (ie, “US $1000 in 1 year”). However, if the “US $500 now” option is selected, the next question will feature the US $1000 reward at a more proximal time (ie, “US $500 now” or “US $1000 in 1 day”). In this way, the reward amount or time will be titrated to identify the rate (ie, k-value) at which the participant discounts monetary rewards over time. The TD rate will be calculated for each participant and then compared across treatment group as a between-subjects variable and as a within-subjects repeated measure variable, comparing the effect of the treatment (baseline compared with after allocation and at closeout).

#### Food Demand

The food demand task will be given at baseline, after allocation, and at closeout. It is based on a food purchasing task [37] that assesses the amount participants are willing to pay (ie, reward value) for different quantities of snack foods. Participants will first view photos of different healthy (eg, apple, yogurt, and popcorn) and unhealthy (eg, potato chips, chocolate chip cookies, and candy bar) snack foods that correspond with the real food items they are presented with in the food choice task (see the Food Choice section below). Participants select their most preferred healthy food and their most preferred unhealthy food from the list and answer the questionnaire for each of the 2 food items. These preferred food photos are displayed on the computer during the task so that participants can refer to them when completing the task. The instructions, modified from the study by Epstein et al [40], are available in Multimedia Appendix 1.

Food demand task responses will be used to generate a food demand curve, reflecting the quantitative relationship between demand for food and escalating price. We will calculate the food demand curve for each of the preferred healthy and unhealthy options. Calculating the food demand curve generates 5 indices: (1) food demand breakpoint (ie, the first price at which consumption was 0), (2) intensity of food demand (ie, consumption at the lowest price), (3) elasticity of food demand (ie, sensitivity of snack food consumption to increases in cost), (4) Omax (ie, maximum expenditure for snack food), and (5) Pmax (ie, price at which expenditure was maximized). Calculating the food demand curve for each of the preferred or chosen healthy and unhealthy options will give rise to 10 values (5 indices for each healthy and unhealthy food categories). The primary index of demand will be intensity of food demand, which will be compared across treatment group as a between-subject variable and as a within-subject repeated measure variable, comparing the effect of the treatment (baseline compared with after allocation and at closeout). However, all indices will be calculated to fully describe the demand curve.

#### Food Choice

Food choice will be assessed by presenting participants with an array of healthy and unhealthy snack options after allocation and at closeout. Participants will be presented with the snack options on a tray, and all items will be presented as pairs (ie, 2 apples, 2 bags of chips, or 2 candy bars) to encourage selection. Participants will be presented with a total of 9 healthy and 9 unhealthy snack options (excluding drink options). Importantly, 2 of each snack option will be presented, so participants will see a total of 18 healthy and 18 unhealthy snack items (36 total snack items). Healthy snack food items have a total calorie count that ranges from 35 to 180 calories per portion. Unhealthy snack food items have a total calorie count that ranges from 230 to 330 calories per portion. An attempt was also made to match items categorically, for example, an unhealthy option such as potato chips will be provided along with a healthy option such as low-calorie popcorn and rice puffs. The snack items will be arranged neatly on the tray and will resemble the snack tray that is sometimes presented to guests in a hotel room. Alongside the tray, participants will be presented with accompanying unhealthy (soda) or healthy (water) drink choices. As with the snack, 2 of each drink option will be available.

Research assistants will describe the availability of the snack options in the context of the requirement that participants fast before the study appointment. This approach is expected to reduce potential participant bias that could occur if participants are aware their food choices will be recorded. The following is a section of the script that research assistants will deliver at this time:

In our lab, we always ask participants not to eat or drink anything before coming into the lab to make sure that differences in how hungry you are or the time since your last meal doesn’t affect your choices on the tasks or your preferences. We know it can be hard to fast and since we ask participants to not eat for two hours before coming in, we like to give people a range of snacks to eat.

Participants will then be encouraged to select any snack option to eat during the session (while completing the final batch of questionnaires) or take the food(s) with them to eat later at their leisure. The research assistant will then leave the participant alone with the snack options while they complete the remaining questionnaire items. All food choices will be recorded by the research assistant after the participant departs. The recorded number of healthy and unhealthy snacks will be summed, respectively, to create *healthy food choice* and *unhealthy food choice* variables for each participant. These variables will be compared across treatment group as a between-subject variable and as a within-subject repeated measure variable, comparing the effect of the treatment (baseline compared with after allocation and at closeout).

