#### Daily Food Diaries

To assess food choice during the 5 days between allocation and closeout, participants will be sent, by email, a link to complete a daily Web-based food diary. This questionnaire is based on the Paffenbarger Physical Activity Questionnaire Dietary Habits subscale [41] and other food frequency questionnaires. Participants will be asked to complete the survey at the end of the day when they do not plan on eating anything afterward. The survey will first ask the participants to briefly describe and/or list the food items or meals they ate that day. Then, participants will be asked to report the number of servings they ate that day for different food categories. The food categories will include fruits; vegetables; grains; eggs; milk and cream; dairy (not including milk); poultry; fish and seafood; beef, pork, lamb, and other red meat; nuts, seeds, and legumes; fats and oils; sweets and desserts (not including candy); candy; salty snacks; drinks; and other foods. For each food category, several examples will be provided to describe what equates to 1 serving of that category. The reported number of daily servings for each of the food categories will be averaged to create a measure of outside-the-lab food intake. For analysis, outside-the-lab food intake will be compared across treatment groups to assess the impact of the intervention arm on outside-the-lab food choices.

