### Analysis

#### Primary Statistical Analysis

Our primary statistical analyses will comprise a mixed design (between-subjects and repeated measure) that compares TD, food demand, and food choice measures at baseline, after allocation, and at closeout across treatment arms. Our analyses will control for standard demographic variables such as age, biological sex, race, and income. A series of repeated measure ANOVAs with treatment arm as a between-subject variable and measurement period as the repeated measure will be conducted on TD rates and healthy and unhealthy food demand indices, respectively.

In addition, to examine the effect of the intervention arms on food choices inside and outside the lab, a series of ANOVAs will be conducted on healthy and unhealthy snack food choices and average daily serving intake values for each of the food categories. To probe the effect of the intervention on in-lab food choices, we will conduct a repeated measure ANOVA with measurement period repeated across treatment group on health and unhealthy snack food choices. Next, to probe the effect of the intervention on food choices outside the lab, we will conduct a 1-way ANOVA with treatment arm entered as the between-subject variable on average daily serving intake values for the primary food categories (ie, fruit and vegetable intake).

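### Snacks taken home from visit 1 can be counted again in the food diary, so a diary difference between arms is not clean evidence of choices made outside the lab

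*Protocol article*

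**What the plan says.** The Food Choice section measures the outcome by "presenting participants with an array of healthy and unhealthy snack options after allocation and at closeout", so the visit 1 tray comes before the diary days. It holds 36 items, 18 healthy and 18 unhealthy, with two units of each option. Participants may eat during the session or "take the food(s) with them to eat later at their leisure". On scoring, the section says: "All food choices will be recorded by the research assistant after the participant departs". Healthy and unhealthy items are then summed. No split between items eaten in the session and items carried away is described.

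The Daily Food Diaries section states its purpose as "To assess food choice during the 5 days between allocation and closeout". Participants report the servings eaten that day by category. The categories include fruits, dairy, sweets and desserts, candy, and salty snacks. For analysis, "outside-the-lab food intake will be compared across treatment groups to assess the impact of the intervention arm on outside-the-lab food choices". Primary Statistical Analysis specifies a one-way ANOVA by arm on "average daily serving intake values for the primary food categories (ie, fruit and vegetable intake"), and the same paragraph also mentions ANOVAs on each of the food categories.

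Table 1 marks the daily food surveys at t1 to t5 and not at time 0, the day of allocation.

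**The concern.** The two outcomes, as defined, can share the same food. A snack selected in the lab just after the audio is scored as in-lab choice. If it is carried home and eaten on a diary day, it is scored again as a serving outside the lab. Nothing shown excludes or flags study-supplied food.

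The overlap would tend to follow the trial's own hypotheses. The section This Study predicts more healthy and fewer unhealthy choices under episodic future thinking and under positive affect, and the positive-affect imagery is about fruit and vegetables. An arm that takes more fruit from the tray could show higher diary fruit intake with no different choice made elsewhere.

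The diary is the only outcome collected away from the lab. At stake is whether a diary difference shows that the effect carries into daily life, or partly repeats the visit 1 tray result.

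**Working it through.** **The plan's own figures.** The article gives no expected diary difference and no diary standard deviation, so there is no stated figure to reproduce on this point. Its 95% power refers to the arm-by-time interaction. With an effect size of 0.17 read as Cohen's f, 124 analysed, 4 arms, 3 periods, an assumed correlation of 0.5 and sphericity, that power comes out at 0.951. It is not affected here.

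**Inputs from the article.** Five diary days (Daily Food Diaries; Table 1); two units of each snack option (Food Choice); payment for at least 3 of 5 diaries (Reimbursements); 31 analysed per arm, 124 in all (Sample Size).

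**Assumptions.** One item is one serving. D is the arm difference in mean items carried away, s the share eaten on diary days, and d the share that merely replaces other food of the same category. The article gives none of these.

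**1. Size of the carry-over.** Shift in mean daily servings = D × s × (1 − d) / 5. With d = 0, the largest case:

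- D = 1: s = 0.25, 0.5 or 1 gives 0.05, 0.10 or 0.20.
- D = 0.5, s = 1: 0.5/5 = 0.10.
- D = 2 (both units of one option), s = 1: 2/5 = 0.40.

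**2. Participants with only three diaries.** An item eaten on a reported day adds 1/3 = 0.33. If the three reported days are unrelated to the day of eating, the chance that it was a reported day is 3/5. The expected addition is (3/5) × (1/3) = 0.20, the same as with five diaries.

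**3. Effect on the one-way ANOVA.** Suppose the two positive-affect arms gain b servings/day from lab snacks and nothing else differs. Then f = b/(2 × SD), the noncentrality is f² × 124, and the degrees of freedom are 3 and 120. For b = 0.10 and SD = 1, this is 0.05² × 124 = 0.31. Probability of p < .05, ignoring covariates:

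| b (servings/day) | SD 1 | SD 1.5 | SD 2 |
|---|---|---|---|
| 0.10 | 6.8% | 5.8% | 5.4% |
| 0.20 | 13.0% | 8.3% | 6.8% |
| 0.40 | 42.5% | 20.3% | 13.0% |

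The SDs and values of b are assumptions. The bottom row needs a mean difference of two whole items, all eaten on diary days with no replacement.

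**4. Which categories are exposed.** The snacks named in the article are apple, yogurt, popcorn, rice puffs, chips, cookies and candy bar. Only the apple falls under fruit or vegetables. The others bear on dairy, salty snacks, sweets, candy or grains. With 9 healthy options on the tray and only some named, other fruit or vegetable items are possible but not shown.

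**The case against.** The strongest case against has five parts.

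- **Silence in a condensed article.** The diary form and the instructions given at visit 1 are not shown and might tell participants to leave out study snacks. This stands as a condition: if they do, the point falls. But the article does define both outcomes, and as defined they overlap.
- **The visit day.** Table 1 places the diaries from t1 on. Snacks eaten in the session, or later that day by people who had just fasted, would appear to escape. This stands and shrinks the share that can carry over.
- **It is real intake.** An apple eaten at home is food eaten outside the lab, and eating it there is partly a choice made there. Every arm sees the same tray and arms are randomized. A reader might infer that the diary comparison is confounded or that the arm difference would be spurious. The documents do not support that: a difference in total intake would still be caused by assignment. Only its interpretation is open.
- **Size.** A reader might take 0.33 or 0.67 servings/day, from one or two items over three diaries, as the likely effect. Step 2 shows that this ignores items eaten on unreported days.
- **Subtraction can mislead.** Removing lab items from the main comparison does not restore the food they replaced and may delete home-bought fruit, most in the arm that ate more fruit. This stands and determines the form of the fix.

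**Conclusion.** The overlap follows from the text and nothing shown removes it. A visit 1 snack eaten on t1 to t5 can count in both outcomes, so a diary difference may partly reflect a choice made in the lab just after the intervention. This is a possibility and not a demonstrated effect: arms must differ in what they carry away, and the food must be eaten on diary days.

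The likely size is modest. Each item eaten on a diary day adds at most 0.20 servings/day in expectation, and an assumed 0.5-item difference gives about 0.10. At 0.10 in two arms the ANOVA would be significant 5.4% to 6.8% of the time under the assumed SDs, against a nominal 5%. The primary fruit and vegetable analysis is exposed only through items such as the apple; the other categories are exposed through dairy, candy, sweets and salty snacks. The sample size is unaffected.

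It would go too far to infer that any diary effect is an artefact of free food. The supported conclusion is that the planned analysis cannot separate the two readings.

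**What to change.** Keep the all-intake diary comparison as planned. Add a sensitivity analysis that excludes lab-supplied items, and report both estimates with confidence intervals.

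- **Remaining participants.** Ask once, at the end of visit 2, which visit 1 snacks they ate and on which day. Ask only after the second food selection is finished, so that the concealment described under Consent Procedure is kept.
- **Completed participants** (84 at submission). Match recorded tray selections to the free-text food list in the diary. This requires that selections were recorded item by item, which the article implies but does not state.
- **Interpretation.** Claim an effect on outside-the-lab choice only if it persists without those items. If lab items are identified correctly, the two estimates bracket the answer: excluding them is right if they replaced nothing, and including them is right if they replaced other food one for one.

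The cost is one short question block and some recoding. The downsides are recall error over about 5 days, approximate matching for those already finished, and possible over-removal because replaced food is not restored. That last point is why this belongs in a sensitivity analysis and not in the main comparison.
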